**Primary Outcomes (Respondent: Adolescent Participant)**			
Viral load/Virologic Suppression*	Biomedical data: Viral load*	n/a	^a^T1-RC, 12, 24, 36, 48
Secondary Outcomes (Respondent: Adolescent Participant)			
Adherence	Self-Report Questionnaire, Pill Counts, adherence self-efficacy [172]		^a^T1-RC, 12, 24, 36, 48
Financial/economic stability (savings and asset accumulation)	Bank statements, MIS IDA, and American Dream Policy Demonstration [173]	n/a	^a^T1-RC, 12, 24, 36, 48
Sexual risk taking behavior:	Time-line Follow Back (TFLB) [174, 175] Adapted Youth Aids Prevention Project (used in Suubi & CHAMP) [176]	n/a	^a^T1-RC, 12, 24, 36, 48
Mental Health Functioning	Center for Epidemiological Studies-Depression Scale (CES-D) [177]	0.65	^a^T1-RC, 12, 24, 36, 48
STIs	Biomedical data: Gonorrhea, Chlamydia, Trichomonas	n/a	^a^T1-RC, 12, 24, 36, 48

^a^T1-RC – Time 1 at reconsenting.

#### Biological assay

To measure Viral load (VL) suppression, we will use the same procedure from *Suubi+Adherence* for Suubi+Adherence-R2: Viral load testing will be done by blood draws at 12-month intervals post-reconsenting. In accordance with the Abbott platform, VL will be dichotomized between undetectable (< 40 copies/ml) and detectable (≥ 40 copies/ml) levels.

In addition to VL, to assess sexual risk-taking behaviors, a secondary outcome, we will test for Gonorrhea, Trichomonas, and Chlamydia. In conducting these tests, collection, counseling, notification, referral for treatment, follow up and monitoring procedures for these biological test—all used in current studies by [name] and colleagues – will be completed at Waves 6 – 10. As recommended by the CDC, we will use the more sensitive NAATs for Chlamydia and Gonorrhea testing. Trichomoniasis will be tested using culture which is considered a current criterion standard. Samples for culture will be obtained using vaginal swabs.

#### Adherence

ART adherence will be assessed by three items that have been used widely in resource limited settings with low-literacy populations addressing: 1) how often they take all of their HIV medications as prescribed, 2) their ability to take all of their medications as prescribed, and 3) how often they missed taking their medications within the past 4-weeks and 6-months [178]. This will be augmented with unannounced pill counts to be conducted at least once every 3 months – as used in *Suubi+Adherence*.

Unannounced pill counts conducted in patients’ homes have demonstrated validity for monitoring medication adherence [3]. Specifically, using the *Suubi+Adherence* protocol for unannounced pill counts [3], the Research Assistant (RA) will follow the following steps [3]: 1) upon visiting the home, ask the participant to bring out all medications in the home, including closed bottles, pillboxes, and doses kept in pockets, purses, backpacks, etc.; 2) ascertain each participant’s regimen before actual counting; 3) in the presence of the participant, thoroughly clean their hands using soap and water, dry their hands using a clean dry towel; 4) using alcohol prep wipes, clean a pharmacy pill tray—that the RA will have– to be used for pill counting; 5) sort the medications into clusters using a spatula; 6) record prescription numbers on each medication, refill date, and dispensed quantity; 7) ask the participant if they had lost or received any pills since their previous count and whether they had taken any of the drug that day; 8) in the presence of the participant, count pills using the study-provided pharmacist tray; and 9) repeat the procedure to double count. Participants will provide times of days they are most likely to be available for pill counts. We will visit participants at an undisclosed time and day to count their pills once every 3 months throughout the study period. Adherence is calculated as the difference between the current and previous pill count divided by the prescribed number of doses for the same period. We have used the same procedures in our *Suubi+Adherence* study. Unannounced pill counts by RAs have been validated in multiple studies with strong association with VL, and has had limited, if any, impact on adherence behaviors [179].

#### Semi-structured qualitative interviews

Two sets of qualitative interviews will be conducted. The first set will be at Wave 6 (Immediately following re-consenting) to explore: 1) participants’ previous experiences with the FEE intervention and its specific components for the treatment group, and their experiences with BSOC for the control group; 2) key multi-level factors (individual, economic, family, contextual, and programmatic) that may have impacted their participation; and 3) key multi-level factors that may have affected their decision-making and behaviors around ART adherence as well as overall mental health since the completion of the *Suubi+Adherence study*. The second set of interviews will be at each follow-up time point (Waves 7-10) to unpack: 1) the longer-term impact, including key multi-level factors affecting participants’ adherence and savings decisions, and mental health as they transition to young adulthood; 2) experiences with social transitions and their potential effect on decision-making around adherence and on mental health; and 3) participants’ perceptions of economic costs and rewards of adherence. A stratified purposeful sampling strategy [180] will be used to randomly select participants from each quartile. Participants in the highest and lowest quartiles on three key outcomes (sexual risk-taking, savings, and mental health) will be invited for interviews (n=80). This sample size will achieve theoretical saturation [181, 182] and will represent ~15% of the participants in each study condition (n=40 for treatment arm; n=40 for BSOC arm). This sampling method will ensure that participants with varying experiences are represented and allow us to identify common patterns and variations in their experiences. Interviews will be conducted in English or Luganda based on participants’ preference. Questions will be translated (English to Luganda) and back-translated by two team members. Questions will be reviewed by two native speakers to ensure they sound natural and conversational. Each interview will last about 60 minutes and will be audio-taped.

### Data Analysis Plan

#### Data quality assurance, initial analyses, and missing data

We will continue to use MIS IDA Q [75] to check for data-entry errors and missing values. Frequency tables for all variables and measures of central tendency and variability for continuous variables will characterize the sample overall and by randomization group. We will address incomplete data with direct maximum likelihood (ML) and multiple imputation (MI) [183] because they make the relatively mild assumption that incomplete data arise from a conditionally missing-at-random (MAR) mechanism [184]. Auxiliary variables will be included to help meet the MAR assumption [185, 186] and sensitivity analyses will be conducted with weighted MI [187] to assess the robustness of the MAR assumption [188]. SAS [189] and M*plus* [190] will be used to perform the analyses.

#### Time points used in inferential analyses

To maximize rigor, to assure alignment of cognitive functioning data (only measured in the *Suubi+Adherence-R2 study*) and our remaining outcomes, and to avoid reuse of *Suubi+Adherence* outcomes (already examined for shorter-term intervention efficacy) that would bias tests of longer-term intervention efficacy, all primary inferential analyses and most of the secondary inferential analyses listed will use only Suubi+*Adherence-R2* data. The exception is longitudinal developmental trajectory analyses to explore associations between changes in time-varying covariates and mechanisms of change with outcomes measured across both *Suubi+Adherence* and *Suubi+Adherence-R2*.

#### Primary Analyses for Aim 1

We hypothesize that participants in the *Suubi+Adherence* intervention group will exhibit a higher odds of HIV viral suppression relative to participants in the bolstered standard of care (BSOC) control condition (H1a) during Suubi+*Adherence-R2*. To test H1a, we will fit a three-level generalized linear mixed model (GLMM) with fixed effects for study arm, time, and their interaction. We will use random intercepts for Clinic ID to account for clustering of persons within clinics and include random intercepts, random slopes, and their covariance for person ID to account for clustering of repeated measurements within persons. Reflecting the binary HIV viral suppression outcome, a binomial distribution and logit link will be used. To test H1a we will perform a time-averaged comparison of repeatedly measured observations across study arms to examine intervention effects over the duration of the study period. Alpha will be set at .05 for this planned comparison.

#### Secondary Exploratory Analyses for Aim 1

We will employ the same three-level GLMM strategy as described above to evaluate the exploratory hypotheses that assess whether the odds of ART adherence and engagement in HIV care are higher in the *Suubi+Adherence* intervention group to the BSOC control group. We will investigate in secondary exploratory analyses whether *Suubi+Adherence* intervention group participants exhibit during Suubi+*Adherence-R2*: H1(b) a higher odds of adhering to the prescribed medication regimen at > 90%; and H1(c) increased odds of keeping all medical appointments in the last 12 months. The same three-level GLMM approach as described above for the primary analysis will be used. Alpha (α) will be set to .05 for each of these exploratory hypotheses. To maximize rigor, quasi-likelihood methods will not be used [191]. Instead, maximum likelihood estimation via adaptive Gaussian quadrature with 15 integration points will be used to ensure stable solutions.

#### Primary Analyses for Aim 2

We anticipate that in the long run and during the social transition period for participants, YLHIV in the intervention group will report superior mean levels of protective health behaviors, improved financial outcomes related to successful uptake of the microfinance-based principles FEE, and lower negative health risk behaviors, as implied by Specific Aim 2. Relative to participants in the BSOC control condition, intervention group participants should, over time/during the transition period: H2(a) exhibit lowered mean levels of sexual risk behavior; H2(b) report increased mean levels of adherence self-efficacy; H2(c) increased mean economic stability; H2(d) increased mean levels of cognitive functioning, and H2(e) increased mean levels of mental health functioning, H2(f) increased mean levels of social support and H2(g) prosocial transition functioning. To test H2(a)-H2(g) we will fit linear mixed models (LMMs) using the same fixed effects (study arm, time, and study arm-by-time) and random effects for the clinic (random intercepts) and person levels (random intercepts, random slopes, and their covariance) as in the proposed H1 analyses described. To maintain a nominal Type 1 error rate of 5% across tests of H2(a)-H2(g), α will be set at .05/7=.007 for each planned time-averaged comparison. To maximize rigor, the assumptions of normality and constant variance of residuals for these continuous outcomes in LMMs will be evaluated by examining histograms of the residuals and scatter plots of predicted values-by-Cholesky-scaled residuals, respectively. Transformations of outcomes will be utilized as needed to improve data conformance with model assumptions. Inferences for models whose residual statistics still do not fully meet assumptions following transformations will be generated via robust heteroskedastic-consistent estimators [192]. All analyses will include outlier and influential case screening via computation of Cook’s D, DFBetas, and likelihood displacement statistics. If outliers are found, results will be reported with and without outliers included [193, 194].

#### Secondary exploratory analyses for Aim 2

The same GLMM approach described above for Aim 1’s primary analysis will be used to test whether the odds of STI acquisition during young adulthood is lower across time for intervention participants than control participants.

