##### Sex as a biological variable

In line with recent NIH guidelines on exploring sex differences in effects, all previously described inferential analyses will be repeated with models extended to include sex assigned at birth as a moderator to examine whether effects vary by participant sex.

#### Statistical Power Analysis for Aims 1 and 2

We used NCSS PASS [199] to compute minimum detectable effect size estimates for the primary hypotheses H1(a) and H2(a)-H2(g) proposed to fulfil Specific Aims 1 and 2, respectively. For all power analyses we assume power=.80 and 5 repeated assessments from N=450 participants conservatively assuming 20% attrition. For H1(a), based on our current *Suubi+Adherence* project’s data we further assumed a control proportion of 65% virally suppressed, α=.05, and an intraclass correlation (ICC) of .032 at the clinic level and .819 at the person level. Under these assumptions, the minimum detectable raw proportion difference is 13%, which corresponds to an odds ratio (OR) of 1.91 and a standardized effect estimate *h*=.29, which is between a small (*h*=.20) and medium (*h*=.50) effect size [200] The minimum detectable OR of 1.91 is less than ORs obtained in the *Suubi+Adherence* study [6] ensuring that we will have sufficient power to detect similar or slightly smaller effects in the project period. For H2(a)-H2(g), we computed the minimum detectable standardized mean difference *d* using the same inputs as listed above, α=.007, and a range of ICCs from .003 to .542 for change mechanisms based on data from the *Suubi+Adherence* study. Under these conditions *d* ranged from .10 to .13, which are small standardized effect sizes [201]. Taken collectively, our study will have sufficient power to detect small to small-medium effects across a wide variety of conditions.

#### Qualitative data analysis for Aim 3

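### The Bonferroni rule for the seven Aim 2 tests is valid, but Holm's step-down procedure gives the same 5% family-wise guarantee and never rejects fewer hypotheses (optional improvement)

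*Protocol article*

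**What the plan says.** Under Primary Analyses for Aim 2, the protocol article lists seven hypotheses: sexual risk behaviour, adherence self-efficacy, economic stability, cognitive functioning, mental health functioning, social support and prosocial transitions. Each is tested by a time-averaged comparison of the arms in a linear mixed model. All seven are worded as expectations in favour of the intervention: "Relative to participants in the BSOC control condition, intervention group participants should, over time/during the transition period" do better on each. The stated aim is a nominal Type 1 error of 5% across the seven tests, and the rule is that "α will be set at .05/7=.007 for each planned time-averaged comparison".

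Statistical Power Analysis for Aims 1 and 2 uses the same level. It assumes "power=.80 and 5 repeated assessments from N=450 participants conservatively assuming 20% attrition" and, for Aim 2, "α=.007, and a range of ICCs from .003 to .542 for change mechanisms". Neither section mentions a step-down or other sequential procedure.

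**The concern.** Under the stated rule, every hypothesis must reach .05/7 however many of the others have already been rejected. The 5% guarantee does not require that. After one rejection, at most six true null hypotheses can remain if no error has yet been made, so the next p-value can be compared with .05/6, and so on.

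The authors expect a benefit on all seven outcomes. That many-effects setting is where a step-down rule helps most. The sample is limited to the original cohort of 702, so power cannot be raised by recruiting. At stake is whether some real mechanism effects go unconfirmed when the same error guarantee would allow them to be claimed. The primary outcome, viral suppression, is not affected.

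**Working it through.** **The plan's figure.** .05/7 = .00714, printed as .007. Seven tests at .007 spend at most 7 × .007 = .049. If the tests were independent, the family-wise error would be 1 − (1 − .007)^7 = .048. The split is correct, and the rounding is in the conservative direction.

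**Holm's thresholds.** Order the p-values from smallest to largest and compare them in turn with .05/7, .05/6, .05/5, .05/4, .05/3, .05/2 and .05/1, that is .0071, .0083, .0100, .0125, .0167, .0250 and .0500. Stop at the first failure.

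**Same guarantee.** Suppose m0 of the seven null hypotheses are true. The first true null that Holm rejects is reached at step 7 − m0 + 1 at the latest, where the threshold is .05/m0. An error therefore requires at least one of m0 true-null p-values to be at or below .05/m0. The probability of that is at most m0 × (.05/m0) = .05, whatever the correlation.

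**Never fewer rejections.** Every Holm threshold is at least .05/7, so any p-value that passes Bonferroni also passes Holm. The first threshold is the same in both, so the chance of at least one rejection is identical.

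**Size of the gain.** Inputs from the article: seven tests, 5% across the family, 80% power. Assumptions, because the article does not give them: two-sided tests, the number of real effects, and a common correlation of 0, .3 or .6 between test statistics. Each real effect has mean z = 2.690 + 0.842 = 3.532, which gives 80% power at two-sided .05/7. Simulation with 400,000 replicates per setting; the three values in each cell are for correlations 0 / .3 / .6.

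| Real effects | Average power, Bonferroni | Gain with Holm, percentage points | Share of real effects with p between .05/7 and .05 that Holm confirms |
|---|---|---|---|
| 1 | 80% | 0.1 or less | 0.4% / 0.4% / 0.2% |
| 2 | 80% | 1.2 / 1.1 / 1.0 | 8% / 8% / 7% |
| 3 | 80% | 2.5 / 2.3 / 2.0 | 18% / 16% / 14% |
| 4 | 80% | 4.0 / 3.6 / 3.2 | 28% / 25% / 23% |
| 7 | 80% | 11.6 / 9.9 / 8.4 | 82% / 70% / 59% |

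Holm rejected everything that Bonferroni rejected in every replicate. Its family-wise error stayed below 5% in every setting. With four real effects and no correlation, it was 4.2% against 2.1% for Bonferroni.

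**What a single p-value needs.** A p-value of .02 passes Holm only if at least five other hypotheses have already been rejected (threshold .025). A p-value of .03 passes only if all six others have been.

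**The case against.** The strongest reply is that nothing in the article is wrong. The rule meets its stated aim, is computed correctly and agrees with the power analysis, and preferring another valid procedure is close to a matter of taste. That stands in full as to validity: there is no bias, no inflated error and no contradiction.

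Three stronger readings are tempting, and none is supported.

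- A reader might infer that Bonferroni is weaker in every situation. It is never stronger, but the chance of at least one rejection is the same under both rules, and with one or two real effects the difference is about one percentage point or less.
- A reader might infer that every real effect with p between .007 and .05 is needlessly lost. Holm confirms under 1% of these with one real effect and about a quarter with four. It confirms most of them only if all seven effects are real.
- A reader might infer that the power is given up for nothing. A fixed threshold yields simple simultaneous confidence intervals that match the decisions, and Holm does not give these directly. Holm also gains by using error that Bonferroni leaves unspent. The article does not announce simultaneous intervals for Aim 2, so this cost is small, but it is not zero.

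The links between the outcomes cut both ways. They make it more plausible that several effects are real together, but correlation between the tests shrinks the gain, from 11.6 to 8.4 points with seven real effects. The chance of confirming all seven rises steeply (from 21% to 63% at zero correlation), but the article sets no such success criterion, so that figure should not carry the argument.

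**Conclusion.** The point holds as an optional improvement. The plan contains no error here. Holm offers the same 5% family-wise guarantee without any further assumption, never rejects fewer hypotheses, and can reject more after the first rejection.

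The benefit is negligible with one real effect, a few percentage points of average power with three or four, and 8 to 12 points only if all seven are real. The ordering of the two procedures is a mathematical fact and does not depend on sidedness or correlation. The size of the gain rests on the assumed number of real effects, the assumed correlation, and each real effect having exactly 80% power at .05/7.

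**What to change.** In Primary Analyses for Aim 2, replace the sentence on the per-test level with: *The family-wise error across H2(a)-H2(g) is held at 5% with the Holm step-down procedure (ordered p-values against .05/7, .05/6, ..., .05).* Fix the change, with a date, before outcomes are compared by arm.

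In Statistical Power Analysis for Aims 1 and 2, keep .05/7 and describe it as the first-step, worst-case threshold. No power calculation has to be redone on account of this change.

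The cost is one sentence. Data collection, sample size and models are untouched. If intervals are reported for the seven comparisons, state that simple simultaneous intervals need not agree with the step-down decisions.

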Following enrolment and baseline assessments, 39 participating clinics were randomly assigned to one of two study groups, resulting in 19 clinics (n = 344 participants) assigned to the control condition and 20 clinics (n = 358 participants) assigned to the intervention condition. A two-arm, cluster randomized trial design was employed where all participants attending the same clinic were assigned to the same study group. All participants received medical Standard of Care (SOC), as defined by the Uganda Ministry of Health guidelines for pediatric and adolescent HIV care and treatment; and psychosocial SOC, consisting of information leaflets on adherence and support provided by lay counsellors including persons living with HIV who have been trained in ART adherence counselling, known as “expert clients”. Due to inconsistency in which SOC is often provided in the region, *Suubi+Adherence* provided youth in both study conditions with a bolstered standard of care (BSOC), which included eight information sessions on adherence to ART, adapting evidence-based, print cartoons to portray adherence topics in a relatable manner [134]. Adolescents in the intervention group received the BSOC as well as a FEE intervention consisting of a Youth Savings Account (YSA), matched at a rate of 1:1 and from which financial savings could be used for medical expenses, family microenterprise development or education related expenses (including school lunches and fees). As part of the YSA package, the intervention group also received four workshops blending FLT and life skills with topics on asset building, IGA, goal setting, and risk mitigation. Data was collected at baseline, 12, 24, 36 and 48- months post-intervention initiation. The study retention rate of 93.4% over a 6-year period (2012-2018).

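### The STI analysis is described as a test of acquisition, but annual tests for current infection can only give the odds of being STI-positive at the visit

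*Protocol article*

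**What the plan says.** The hypothesis under Secondary exploratory analyses for Aim 2 is to "test whether the odds of STI acquisition during young adulthood is lower across time for intervention participants than control participants". For the method, "The same GLMM approach described above for Aim 1’s primary analysis will be used". In Primary Analyses for Aim 1 that is a three-level logistic mixed model in which "we will perform a time-averaged comparison of repeatedly measured observations across study arms".

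Table 2 gives one data source for the STI outcome: "Biomedical data: Gonorrhea, Chlamydia, Trichomonas". The Biological assay section adds that "we will use the more sensitive NAATs for Chlamydia and Gonorrhea testing" and that "Trichomoniasis will be tested using culture". It places the tests at Waves 6 to 10, and the Data collection section puts the interviews 12 months apart. Wave 6 is the re-consent wave, and no STI test before it is described.

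The Biological assay section also covers "collection, counseling, notification, referral for treatment, follow up and monitoring procedures for these biological test", with no difference by arm stated. It presents the STI tests as a way to assess sexual risk-taking.

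**The concern.** The quantity named and the data named do not match. Acquisition is a new infection over an interval. NAAT and culture record whether infection is present when the sample is taken. An infection acquired and cleared between two annual visits never appears, and a positive at Wave 6 has no earlier test to date it against. The odds of a positive result therefore mix incidence with duration of infection.

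This matters for the arm comparison if duration differs by arm. The article gives some reason to think it might. The original intervention arm had accounts "from which financial savings could be used for medical expenses", and H1(c) expects that arm to keep its medical appointments more often. A lower positive rate that came from earlier treatment would, with the outcome described as written, be reported as fewer infections acquired. Because the assays are meant to reflect sexual risk-taking, it could then be read as lower sexual risk.

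**Working it through.** The article gives no STI rate, effect size or power figure, so there is none to reproduce.

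**Inputs**
- From the article: five annual tests (Waves 6 to 10), a time-averaged arm contrast, and referral of positives for treatment in both arms.
- Assumed, because the article gives none: incidence λ of 3 to 20 per 100 person-years, equal in the two arms; exponential duration with mean D years, so clearance rate m = 1/D; every positive cured after each wave.

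**Formulas**
- Wave 6, steady state: prevalence = λ/(λ+m). The odds are λ × D, so at equal incidence the odds ratio (OR) is the ratio of durations.
- Waves 7 to 10, everyone clear after the previous wave: prevalence = λ/(λ+m) × (1 − exp(−(λ+m))).
- Time-averaged OR = exp of the mean log OR over the five waves.

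**Worked case, λ = 0.10, control versus intervention**

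| Mean duration | Wave 6 prevalence | Wave 6 OR | Waves 7–10 prevalence | Waves 7–10 OR | Time-averaged OR |
|---|---|---|---|---|---|
| 6 vs 6 months | 4.8% vs 4.8% | 1.00 | 4.2% vs 4.2% | 1.00 | 1.00 |
| 6 vs 5 months | 4.8% vs 4.0% | 0.83 | 4.2% vs 3.7% | 0.87 | 0.87 |
| 6 vs 4 months | 4.8% vs 3.2% | 0.67 | 4.2% vs 3.1% | 0.73 | 0.72 |
| 6 vs 3 months | 4.8% vs 2.4% | 0.50 | 4.2% vs 2.4% | 0.56 | 0.55 |
| 12 vs 9 months | 9.1% vs 7.0% | 0.75 | 6.1% vs 5.3% | 0.87 | 0.84 |
| 12 vs 6 months | 9.1% vs 4.8% | 0.50 | 6.1% vs 4.2% | 0.68 | 0.64 |

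For 6 versus 4 months the last step is (ln 0.667 + 4 × ln 0.729)/5 = (−0.405 − 1.264)/5 = −0.334, and exp(−0.334) = 0.72.

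Over 3 to 20 per 100 person-years the time-averaged ORs move by about 0.01 at most. For 6 versus 4 months the range is 0.71 to 0.72.

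**Infections missed.** The share of a year's new infections still positive at the visit is the Waves 7–10 prevalence divided by λ. Over the same incidence range it is 40–43% at a mean duration of 6 months and 23–24% at 3 months.

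**Infections carried over.** The chance that an untreated infection lasts a full year is exp(−1/D): exp(−2) = 14% at 6 months and exp(−4) = 2% at 3 months. Repeat counting of one infection is therefore uncommon at these durations, even without treatment.

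**The case against.** Several points on the other side have weight.

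- **Faster treatment is not documented.** A reader might infer from the savings accounts that intervention participants clear infections sooner, so that the comparison is biased in their favour. The documents do not support that. They say only that savings in the original study could go to medical costs, among other uses, and that better appointment keeping is a hypothesis. Round 2 adds no matching, and mean savings at 24 months were $19.34 against $4.44. This stands: the arm difference is a possibility, and equal durations give an OR of 1.00.
- **Carry-over and old infections are small matters.** A reader might also infer that persistent infections are widely counted twice, or that Wave 6 positives are mostly old. With 2–14% lasting a year, about 86–98% of Wave 6 positives would have been acquired in the year before. This stands for durations of 3 to 6 months.
- **Referral reduces the distortion.** Treating positives in both arms brings later positives closer to new infections. An untreated steady state at all five waves would give 0.67 and 0.50 for 6 versus 4 and 6 versus 3 months. Allowing for treatment gives about 0.72 and 0.55. The effect shrinks but does not vanish.
- **Sexual risk does not rest on STI results.** H2(a) tests it directly from behavioural measures, and access to services is a listed mechanism in the planned mediation work. This limits the damage but does not correct the name of the STI outcome.
- **Coding may be in an unseen analysis plan.** A rule for new infections could be there. But the article itself states the quantity, the data source and the model, and these do not fit together as written.

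**Conclusion.** The point holds as a mismatch between the quantity claimed and the data collected. As written, the model estimates the odds of being STI-positive at an annual visit, and a conclusion about acquisition would go beyond it. The mislabelling does not depend on any assumption about the arms.

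The further step, a spurious arm difference, is conditional. It needs shorter infections in the intervention arm, and its size rests on assumed durations, equal incidence and full cure of positives after each wave. On those terms the time-averaged OR is about 0.72 for 6 versus 4 months and 0.55 for 6 versus 3 months, and nearer 1 for smaller gaps (0.87 for 6 versus 5 months).

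The analysis is secondary and exploratory, so the severity is minor.

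**What to change.** - Name the outcome *STI positive at the annual visit (point prevalence)* and limit the conclusion to that. Do not read it alone as fewer acquisitions or lower sexual risk.
- As a sensitivity analysis, fit the same mixed model to positives at Waves 7 to 10 that follow a negative or a documented treated result at the previous wave. Report Wave 6 positives separately as prevalent.
- State with that analysis that infections acquired and cleared between visits are still missed, so some dependence on duration remains.
- If between-visit STI diagnosis or treatment is asked about, report it separately by arm as a measure of care-seeking. Do not merge it into the acquisition outcome: it rises with access to care and would bring in detection bias by arm.

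The cost is a change of wording and one derived variable, plus an interview item if the last step is taken. The downside is that the sensitivity analysis loses Wave 6 and some precision.
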